These data are consistent with the results of an NIH pulmonary hypertension screening study. 195 adult patients with sickle cell disease were recruited from the greater Washington, DC region. All patients were screened with transthoracic echocardiograms and the tricuspid regurgitant jet velocity (TRV) was used to estimate the pulmonary artery systolic pressure. Pulmonary hypertension was prospectively defined by a TRV  $\geq$  2.5 m/s and moderate-to-severe PH defined by a TRV  $\geq$  3.0 m/s. Right heart catheterization was performed in consenting patients with TRV  $\geq$  2.8 m/s. This study revealed that 32% of patients with SCD had elevated pulmonary artery systolic pressure (TRV  $\geq$  2.5 m/s) and 9% had at least moderately elevated pressures (TRV  $\geq$  3.0 m/s). Multiple logistic regression analysis identified a history of renal or cardiovascular complications, increased systemic systolic blood pressure, markers of hemolysis (LDH), elevated alkaline phosphatase, and low transferrin levels as independent predictors of PH. Most importantly, TRV of at least 2.5 m/s, as compared to a velocity  $<$  2.5 m/s, was associated with an increased risk of death (RR 10.1; 95% CI, 2.2-47;  $P < 0.001$ ) and remained so after adjustment for other possible risk-factors in proportional hazards regression analysis. The 18 month mortality approached 20% for patients with a TRV  $\geq$  2.5 m/s. In another recent prospective study of 60 patients systematically sampled at a comprehensive sickle cell treatment center, the prevalence of PH (defined by an age and body-mass index adjusted nomogram) was 30 %. Further updated follow-up data from our cohort continues to demonstrate that PH is a strong independent risk factor for mortality with 45-month mortality rate of approximately 40 %. From Cox regression analysis the estimated risk ratio of death, relative to patients with TRV  $<$  2.5 m/s, was 4.4 (95% CI 1.6 to 12.2;  $P < 0.001$ ) for patients with TRV 2.5 to  $<$  3.0 m/s and 10.6 (95% CI 3.3 to 33.6;  $P < 0.001$ ) for patients with TRV  $>$  3.0 m/s. In addition, a study by De Castro and colleagues presented at the meeting of the American Society of Hematology reported a similar prevalence of PH and a remarkably similar 17% mortality rate for patients with PH over 2 years compared with approximately 2% for subjects without pulmonary hypertension. Ataga and colleagues have also shown a 10% mortality rate for patients with PH over 26 months in comparison to 1% in those patients without PH. Taken together, the retrospective and prospective studies strongly support the contention that PH is the greatest risk factor facing the aging population of patients with sickle cell disease and likely patients with other chronic hemolytic disorders.

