### **11.3 Safety Analyses**

All safety analyses will be performed using the ITT/SAF population. Safety variables will include laboratory variables and adverse event information. Specific endpoints that will be examined include:

- Incidence of AEs between baseline and Week 16
- Incidence of SAEs between baseline and Week 16
- Mortality incidence

The primary safety outcomes for the MIT will be all AEs; the subset of AEs defined as SAEs; and mortality. Treatment emergent AEs (those that begin or worsen after start of study drug), drug-related AEs, SAEs, and drug-related SAEs (as determined by the investigator) will be categorized by body system and MedDRA (Version 6.0 or later) preferred term.

The assessment of safety data will be based mainly on the tabulation of AEs, by TRV stratum and treatment arm. Additionally, AEs will be tabulated by severity and relationship to drug. Serious AEs will be described in detail. Comparisons across treatment groups, stratifying on TRV stratum will be made using a Cochran-Mantel-Haenszel chi-square test (or Fisher's Exact test as appropriate) on any AEs that occur in more than 10% of the subjects.

Additionally, continuous blood chemistry and hematology laboratory measurements will be categorized as normal/abnormal and summarized using shift tables, which describe changes in the values across visits.

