## 11.6 Sample Size

This study will randomize 132 subjects (66 to sildenafil and 66 to placebo). Sample size was determined based on the following considerations.

The measurement of primary interest is the change in 6MW distance from baseline to week 16. To estimate the trial sample size for the primary endpoint, we used data from Ghofrani's evaluation of the effects of sildenafil in subjects with chronic thromboembolic pulmonary hypertension. Ghofrani's study showed an average change from baseline of 53.7m in 6MW distance with a standard deviation of 67m after approximately 6 months of sildenafil treatment.

A t-test was used to compare the difference in change from baseline 6MW distance between the sildenafil and placebo treatment groups. In order to calculate the sample size the following assumptions were made:

- No subjects discontinue because of clinical worsening or death
- No subjects dropout prior to week 10 for other reasons
- Sixteen-week change in 6MW distance is normally distributed in both treatment groups
- Sixteen-week change in 6MW distance is 40m in subjects on sildenafil and there is no change in subjects on placebo (i.e., a difference of 40m between the two treatment groups)
- Standard deviation of change from baseline between 62 and 72m for the 16-week change in each of the treatment groups
- Power ranges from 80% to 90%
- Two-sided t-test with  $\alpha=0.05$

Table 6 presents the number of subjects needed per treatment arm for the range of assumed standard deviations and powers, thus the total number is 2 times the numbers presented in each cell.

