**Hematology (Sickle Cell Anemia)**

- Anemia and its complications; chronic simple or exchange transfusion in transfusion program for anemia
- Transfusion reactions
- Treatable infections from bacteria, viruses, protozoa and fungi.
- Mild vaso-occlusive crisis requiring oral narcotic analgesia
- Vaso-occlusive crisis requiring hospital admission
- Avascular necrosis of the femoral head
- New leg ulcers

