#### **Hematology (Sickle Cell Anemia)**

- Priapism requiring medical or surgical intervention
- Acute chest syndrome/pneumonia requiring simple or exchange transfusion, admission and antibiotic therapy (not mechanical ventilation)
- Infections from bacteria, viruses, protozoa and fungi requiring vasopressor support or hospital admission
- Avascular necrosis of the femoral head requiring surgical intervention

- Bleeding requiring transfusion
- Major bleeding complication including intracerebral hemorrhage, stroke or GI bleed
- Sustained thrombocytopenia or neutropenia
- New leg ulcers requiring surgical intervention
- Greater than two admissions for vaso-occlusive crisis per week for two sequential weeks
- Retinal detachment or vitreous bleeding
- Pulmonary embolism
- All hospitalizations for medical indications (with the exception of hospitalizations for vaso-occlusive crises – per Section 13.7.1)

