## **13.8 Reporting of Serious Safety Issues to the DSMB; Suspension Guidelines**

Serious safety issues that arise in this study will be brought to the attention of the Data and Safety Monitoring Board (DSMB), which will make recommendations to the National Heart, Lung, and Blood Institute (NHLBI) regarding possible suspension or termination of the study. The NHLBI will consider the DSMB's recommendations, determine an appropriate action and notify the Data Coordinating Center (DCC). The DCC will notify all participating investigators, who will implement the actions directed by the NHLBI. This section defines "serious safety issues" and describes procedures for bringing them to the attention of the DSMB.

The DCC or PI will make the following types of reports that can alert the DSMB to a potential safety issue:

- Ad hoc reports of unexpected serious adverse events and those serious adverse events associated with major bleeding that are made within 7 or 15 calendar days, as specified in subsequent paragraphs.

- Reports of quarterly statistical analyses of all serious adverse events. The DCC will make such analyses quarterly, but files a report to the DSMB only when analyses indicate that a safety issue has arisen, as defined by the “alert” criteria.
- Reports of semi-annual DCC analyses of all adverse events and of adverse clinical laboratory trends. These reports will highlight any safety issues revealed by the analyses that meet the “alert” criteria.

The DCC will submit the DSMB report to the Chair of the DSMB Subcommittee appointed to monitor this study and to the NHLBI Project Officer and will submit the unexpected SAE report to all study investigators. Each CI will submit the unexpected SAE report to the local Institutional Review Board (IRB) and other local authorities in accordance with the institution’s regulations.

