### **13.8.1 Reporting of All Serious Adverse Events to the DSMB**

Three months after the first subject is enrolled in the study, and at the end of each 3 month period thereafter, if any SAEs (expected or unexpected) have been reported in the study during the preceding 3 months, the DCC will:

- Use the current version of the MedDRA dictionary to code all AEs (serious or not) that have been recorded on study AE forms.
- Make a “snapshot” copy of the adverse events data, including MedDRA codes.
- Create frequency tables of treatment x occurrence (yes or no, since inception of the study) of all subjects. One table will be created for each highest-level MedDRA term for which SAEs have been reported. The counting units are subjects, not events.
- Compute Fisher’s Exact Test (FET) statistic to test the alternative hypothesis that occurrence of SAEs is not independent of treatment group. The FET p-value is not adjusted for multiplicity.
- If the FET p-value is less than the critical value shown in Table 12 and the active treatment group has a higher AE rate, the DCC will conduct further statistical analyses as indicated by the circumstances and report the results to the Chair of the DSMB subcommittee monitoring this study, the PI, and the NHLBI Project Officer.

The DCC will not file a report of all SAEs if none of the FET p-values is less than the critical value shown in Table 12 or if the relative risk is less than 1.

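### Table 12 has no all-cause death row and no pooled SAE criterion, and section 13.8.1 withholds the quarterly SAE report unless one MedDRA class reaches p<0.01, so an excess of deaths from expected conditions could reach the DSMB late

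*Protocol*

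**What the plan says.** - **Outcomes.** Section 11.3: "The primary safety outcomes for the MIT will be all AEs; the subset of AEs defined as SAEs; and mortality".
- **Case-by-case reports to the DSMB.** Section 13.8 limits these to "Ad hoc reports of unexpected serious adverse events and those serious adverse events associated with major bleeding". Table 12 sends unexpected fatal or life-threatening SAEs within 7 calendar days and other unexpected SAEs and serious bleeding within 15.
- **What counts as expected.** Table 11 lists, among others, acute chest syndrome, septicemia, pulmonary embolism, pulmonary hypertension, vaso-occlusive pain and sickle cell hospitalizations longer than 24 hours. Section 13.6.1 leaves expectedness to the Product Safety Team. Nothing says whether a fatal outcome makes a listed event unexpected.
- **Quarterly test.** Section 13.8.1 applies Fisher's exact test to subjects, not events: "One table will be created for each highest-level MedDRA term for which SAEs have been reported". Table 12 sets the critical value at p<0.01, unadjusted, and requires the active arm to be worse.
- **Filing rule.** "The DCC will not file a report of all SAEs if none of the FET p-values is less than the critical value". The second bullet of section 13.8 and the SAE row of Table 12 say the same.
- **Other routes.** Semi-annual adverse event reports (13.8.2, Table 12) and a report about two weeks before each DSMB meeting (13.10.1) do not depend on a threshold.

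**The concern.** The quarterly route is the one that should bridge the gap between semi-annual reports, and it is silent unless a single class crosses p<0.01. Deaths are not tabulated as such. Within a class they are mixed with non-fatal SAEs, and across classes they are divided according to the coded cause. In this population a death would often be attributed to a condition on the expected list, and such a death may never travel the 7-day route. Recruitment of about 13 months plus 16 weeks of treatment (3.7 months) ends near month 17, so only the 6- and 12-month semi-annual reports fall inside the treatment period. An imbalance that emerges between them could wait months unless the DSMB happens to meet.

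**Working it through.** The protocol gives no detection probability for its alert, so there is none to reproduce. The arm size does reproduce: 60 per arm plus 10% is 66, matching "This study will randomize 132 subjects (66 to sildenafil and 66 to placebo".

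**1. Smallest imbalance that alerts.** With equal arms and all events on one side, the two-sided Fisher p-value is 2 × C(66,k)/C(132,k).
- k=7: p=0.0132, no alert.
- k=8: p=0.0062, alert.
- With events on placebo too, the first alerts at 66 per arm are 10 vs 1, 12 vs 2, 14 vs 3 and 24 vs 10.
- At 33 per arm, 7 vs 0 gives p=0.011, so 8 vs 0 is needed there as well.

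All these counts must fall in one MedDRA class.

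**2. Deaths to expect.** Section 2.1 gives several mortality figures; for the NIH screening cohort, "The 18 month mortality approached 20% for patients with a TRV" of at least 2.5 m/s. I assume a constant hazard, h = −ln(1−S)/m for mortality S at m months, and 16 weeks = 16/52 × 12 = 3.69 months. The 16-week risk is then 1 − exp(−3.69h).

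| Protocol figure | 16-week risk | Deaths in 132 |
|---|---|---|
| 10% at 26 months | 1.5% | 2.0 |
| 17% at 2 years | 2.8% | 3.7 |
| 40% at 45 months (NIH cohort, later follow-up) | 4.1% | 5.4 |
| 20% at 18 months (NIH cohort) | 4.5% | 5.9 |
| 40% at 22 months | 8.2% | 10.8 |
| 50% at 2 years | 10.1% | 13.3 |

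Two statements in section 2.1 are set aside. One is a mean survival of 2.5 years in patients who also had chronic lung disease. The other is a conference figure of 30% at two months, which would scale to 48% and is far from the rest.

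**3. Probability of an alert on deaths.** This is the exact sum over two binomials of all outcomes with Fisher p<0.01 and the active arm worse, with every death in one class and no other SAEs there.
- 13.2% vs 4.4% (a tripling of a rate near the NIH cohort's): 1.7% at 33 per arm, 14.1% at 66.
- 5% vs 10%: 3% at 66 per arm.
- 5% vs 15%: 18% at 66 per arm.

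A simulation of six quarterly looks (uniform 13-month accrual, constant hazard, 3,000 runs) at 5% vs 15% gives 22% with one class and 3% with deaths spread evenly over three.

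**4. Probability of an alert on an expected SAE such as crisis admission.** The protocol gives no rates, so these are assumptions. Same method, one class, 66 per arm (placebo vs active):
- 10- to 15-point excess: 11% (10 vs 20), 24% (15 vs 30), 31% (10 vs 25; 9% at 33 per arm).
- 20-point excess: 41% (20 vs 40), 46% (15 vs 35).
- 25- to 30-point excess: 64% (20 vs 45), 79% (30 vs 60).

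**5. What pooling alone would do.** Over six looks at 5% vs 15%, a pooled table at p<0.01 alerts with probability 23%, against 3% when split over three classes. Pooling removes the dilution but leaves power low.

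**The case against.** Several stronger readings are tempting, and the protocol does not support them.

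- **That SAEs have no DSMB alert.** Table 12 has a row for all SAEs. What it lacks is a pooled criterion.
- **That every death from a Table 11 condition bypasses the 7-day route.** Death is not itself a listed term and expectedness is judged SAE by SAE, so such a death might be classed as unexpected. The text leaves this open, which is a reason to settle it and not proof of exclusion.
- **That the DSMB would be blind.** It receives unconditional semi-annual and pre-meeting reports, sets its own review frequency and works under a charter that is not shown and may cover deaths. Every SAE also reaches the coordinating center by the end of the next business day, with medical monitor review.
- **That sections 11.3 and 13.8 contradict each other.** Naming an outcome for the trial analysis does not promise an alert rule for it.
- **That any excess of crisis admissions would be missed.** This holds for moderate excesses, for the half-way point, or if coding spreads events over classes. A 25- to 30-point excess in one class would more likely than not alert by the end.
- **That the IRB rules are part of the gap.** Section 13.7.1 exempts "Vaso-occlusive crisis requiring hospital admission" from IRB reporting, and section 13.7.2 sets the IRB trigger at "Greater than two admissions for vaso-occlusive crisis per week for two sequential weeks". These govern reports to IRBs, not to the DSMB, and no change to them follows from this point.

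It is also fair that the mortality figures come from cohorts unlike the randomized population, which excludes unstable patients and requires a walk of 150 to 500 m. That is why a range is shown. None of this alters the filing rule or the 8 vs 0 threshold.

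**Conclusion.** The concern holds as a weakness of timing and design. The thresholds in step 1 follow from the protocol's own test, critical value and arm size. Seven deaths on sildenafil and none on placebo, more than the 5 to 6 deaths in the whole trial that the NIH cohort rate implies, would not trigger the quarterly report. The alert probabilities for deaths (about 2% half-way and 14% at full enrolment for a tripling) rest on a constant hazard, an assumed placebo rate of 4.4%, full 16-week exposure of the subjects counted, and all deaths in one class; spreading over classes lowers them. The figures for expected SAEs rest on rates that the protocol does not give. The gap for deaths depends on fatal outcomes of listed events being treated as expected, which the text neither states nor rules out. The change is worth making because the stated rule holds back by-arm safety data at almost no saving.

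**What to change.** 1. **Table 12 and section 13.8:** add a row alerting on every case for *All deaths, regardless of expectedness or relationship*, on the 7-day route. This also settles the status of fatal listed events.
2. **Section 13.8.1:** delete the sentence that withholds the quarterly report, and send the by-arm SAE table to the DSMB chair every quarter whatever the p-values. Align the second bullet of section 13.8, the conditional reporting step in 13.8.1 and the SAE row of Table 12. The p<0.01 rule can stay as the trigger for further analysis.
3. **Quarterly table:** add pooled rows for all-cause death and for any SAE. Because pooling leaves power low at p<0.01, items 1 and 2 do most of the work.

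The cost is a wording amendment, two rows in an existing program, a quarterly transmission, and at most about 2 to 13 case reports on the scaled rates above, fewer where a death is already reported as unexpected. The downside is some extra review and an occasional chance alert from the added rows.

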### **13.8.2 Reporting of All Adverse Events (Serious and Non-serious)**

Six months after the first subject is enrolled in the study, and at the end of each 6 month period thereafter, the DCC will:

- Use the current version of the Medical Dictionary for Regulatory Activities (MedDRA) to code all AEs that have been recorded on study AE forms.
- Make a “snapshot” copy of the adverse events data, including MedDRA codes.

- Create frequency tables of treatment x occurrence (yes or no, since inception of the study) of all subjects. One table will be created for each highest-level MedDRA term for which AEs have been reported. The counting units are subjects, not events.
- Compute Fisher's Exact Test (FET) statistic to test the alternative hypothesis that occurrence of AEs is not independent of treatment group. The FET p-value is not adjusted for multiplicity.
- If the FET p-value is less than the critical value shown in Table 12 and the active treatment group has a higher AE rate, the DCC will conduct further statistical analyses as indicated by the circumstances and alert the DSMB to this finding in the semi-annual DSMB report.
- Collaborate with the PI to incorporate the results into the study's semi-annual report to the DSMB and the NHLBI Project Officer.
- A copy of the study's semi-annual report will be submitted to the IND Holder's IRB. Measures will be taken to ensure that the PI and Study Coordinator at that site remain blinded to their subject's treatment.

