#### ***12.3.2.2 Adverse Reactions: Pre-marketing Experience***

Sildenafil was administered to over 3700 patients (aged 19-87 years) during clinical trials worldwide. Over 550 patients were treated for longer than one year.

In placebo-controlled clinical studies, the discontinuation rate due to adverse events for sildenafil (2.5%) was not significantly different from placebo (2.3%). The adverse events were generally transient and mild to moderate in nature.

In trials of all designs, adverse events reported by patients receiving sildenafil were generally similar. In fixed-dose studies, the incidence of some adverse events increased with dose. The nature of the adverse events in flexible-dose studies, which more closely reflect the recommended dosage regimen, was similar to that for fixed-dose studies.

When sildenafil was taken as recommended (on an as-needed basis) in flexible-dose, placebo-controlled clinical trials, the following adverse events were reported:

**Table 8. Adverse Events Reported more Frequently by Patients Treated with Sildenafil than those Treated with Placebo in PRN Flexible-Dose Phase II/III Studies**

| Event                        | Percentage of Patients Reporting an Event  |                  |
|------------------------------|--------------------------------------------------------|------------------|
|                              | SILDENAFIL
N=734                                    | PLACEBO
N=725 |
| Headache                     | 16%                                                    | 4%               |
| Flushing                     | 10%                                                    | 1%               |
| Dyspepsia                    | 7%                                                     | 2%               |
| Nasal Congestion             | 4%                                                     | 2%               |
| Urinary Tract Infection      | 3%                                                     | 2%               |
| Abnormal Vision  | 3%                                                     | 0%               |
| Diarrhea                     | 3%                                                     | 1%               |
| Dizziness                    | 2%                                                     | 1%               |
| Rash                         | 2%                                                     | 1%               |

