|-------------------------------------------|------------------------------------------------------------------------------------------------------------------------------------------------------------------------------------------------------------------------------------------------------------------------------------------------------------------------------------------------------|--------------------------------------------------|
| Unexpected SAEs                           | Clinical investigator notifies DCC SAE Regulatory Specialist and PI.
Clinical investigator, DCC SAE Regulatory Specialist and PI prepare report using FDA forms and submit report to DSMB, NHLBI Project Officer, IRBs, study investigators. Report:
Fatal or life-threatening: within 7 calendar days.
Otherwise: within 15 calendar days. | Alert all cases.                                 |
| Serious Bleeding Events, other than above | Clinical investigator notifies DCC SAE Regulatory Specialist and PI.
Clinical investigator, DCC SAE Regulatory Specialist and PI prepare report and submit report to DSMB and NHLBI Project Officer within 15 calendar days                                                                                                                       | Alert all cases.                                 |
| All SAEs                                  | DCC performs quarterly analyses of MedDRA-coded SAEs, tabulates subjects with SAEs classified by highest-level MedDRA term. Report only when $p <$ critical value and active treatment group has higher AE rate.                                                                                                                                     | $p < 0.01$
$p$ not adjusted for multiplicity  |
| Adverse Events (all)                      | DCC performs semi-annual analyses of MedDRA-coded AEs, tabulates subjects with AEs classified by highest-level MedDRA term. Report every 6 months. Alert only when FET $p <$ critical value and active treatment group has higher AE rate.                                                                                                           | $p < 0.01$
$p$ not adjusted for multiplicity  |

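### The DSMB adverse-event alert is tested only at the highest MedDRA level, which dilutes a specific harm and, for expected non-bleeding SAEs, also decides whether the quarterly report is filed

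*Protocol*

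**What the plan says.** Section 13.8.2 sets out the semi-annual look at all adverse events. The DCC codes the events and counts subjects rather than events: "One table will be created for each highest-level MedDRA term for which AEs have been reported". It then uses Fisher's exact test to "test the alternative hypothesis that occurrence of AEs is not independent of treatment group". Section 13.8.1 uses the same construction each quarter for serious events: "One table will be created for each highest-level MedDRA term for which SAEs have been reported". In Table 12 the row for all adverse events says that the DCC "tabulates subjects with AEs classified by highest-level MedDRA term" and adds: "Alert only when FET $p <$ critical value and active treatment group has higher AE rate". The critical value is 0.01, unadjusted, in both rows. In both sections, further statistical analyses follow only after that threshold is crossed.

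Two features of section 13.8 bear on the consequences:

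- The semi-annual report is sent whether or not there is an alert. The quarterly SAE report is not filed if no class-level p-value falls below the critical value.
- Unexpected SAEs and serious bleeding events are alerted case by case.

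Elsewhere the protocol works at a finer level. In section 11.3, treatment-emergent and serious events "will be categorized by body system and MedDRA (Version 6.0 or later) preferred term". Table 8 in section 12.3.2.2 lists individual events under the title "Adverse Events Reported more Frequently by Patients Treated with Sildenafil than those Treated with Placebo". Priapism (4.4.2.3), visual change (7.1), and headache and facial edema (7.2) each have their own monitoring, discontinuation or dose provisions.

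**The concern.** The alert asks whether a subject had any event in a body system. A subject already counted for an unrelated event adds nothing if the drug-related event also occurs, so the difference between arms shrinks while its variance usually grows. Sickle cell disease produces events in many body systems, as the long list in Table 11 shows, so some background is plausible in many classes. For priapism the tables are also built on all subjects, so females enter the denominator.

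At stake is how readily a particular harm is drawn to the DSMB's attention during the trial. For non-serious events the test decides only what is highlighted. For expected SAEs other than serious bleeding it decides more. Section 13.6.2 and Table 11 class events such as acute chest syndrome and vaso-occlusive pain as expected, so they have no case-by-case route to the DSMB in 13.8. Their quarterly report depends on the pooled test.

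**Working it through.** **Inputs from the protocol.** Section 11.6: "This study will randomize 132 subjects (66 to sildenafil and 66 to placebo"). Table 12: p<0.01, active arm higher. Table 8: headache 16% v 4%, flushing 10% v 1%, dyspepsia 7% v 2%, abnormal vision 3% v 0%.

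**Assumptions.** The share b of each arm with an unrelated event in the same class is not given. I take b from 10% to 40%, equal in both arms and independent of the drug event, with wider values where noted. An interim look at half enrolment, 33 per arm, is also assumed.

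**The plan's own figure.** The protocol states no operating characteristics for the alert, so the related figure to reproduce is the sample size. For a 40 m difference, SD 67 m, 90% power and two-sided 0.05, n = 2 × (1.960 + 1.282)² × 67²/40² = 2 × 10.51 × 2.806 ≈ 59 per arm by the normal approximation. The t-test gives 59.94, so 60, and 60 × 1.10 = 66. This agrees with section 11.6.

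**Method.** With X and Y the subjects with an event on sildenafil and placebo, binomial with n = 66, the alert probability is the sum of P(X=x)P(Y=y) over all pairs with x > y and two-sided Fisher p<0.01. At event level the rates are the Table 8 rates. At class level each rate p becomes 1 − (1 − p)(1 − b).

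**Example, headache with b = 20%.** Sildenafil: 1 − 0.84 × 0.80 = 32.8%. Placebo: 1 − 0.96 × 0.80 = 23.2%. The 12-point excess becomes 9.6 points on a much higher base rate.

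**Results, probability of an alert at 66 per arm:**

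| True event rates | Event level | b = 10% | b = 20% | b = 30% | b = 40% |
|---|---|---|---|---|---|
| 16% v 4% (headache) | 31% | 11% | 6% | 4% | 3% |
| 10% v 1% (flushing) | 22% | 6% | 3% | 2% | 2% |
| 30% v 4% (illustrative) | 93% | 65% | 42% | 27% | 18% |
| 50% v 10% (illustrative) | 99.5% | 95% | 85% | 71% | 53% |

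**Limits of event-level testing.** Dyspepsia at Table 8 rates alerts 3% of the time and abnormal vision 0.1%, even when tested alone. With no placebo events, 7 v 0 gives p = 0.013 and 8 v 0 gives p = 0.006, so eight sildenafil subjects are the minimum. With one placebo event the minimum is 10 v 1.

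**Interim look.** At 33 per arm, headache alerts with probability 5% at event level and 3%, 2%, 2% and 1% at b = 10%, 20%, 30% and 40%.

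**False alerts.** With equal true rates in both arms and 66 per arm, the same sum gives 0.08% at a common rate of 5%, 0.23% at 10% and 0.29% at 30%, so about 0.3% or less per test per look at event rates up to 30%.

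**The case against.** The strongest reply is that the alert is a screening flag, not the DSMB's only source of information. The semi-annual report goes every six months without any threshold, unexpected SAEs and serious bleeding are reported individually, laboratory trends have their own test, and section 13.10.1 has the DSMB receiving relevant safety information under its own charter. Nothing confines the DSMB to class tables. All of this stands. It confines the serious part of the gap to expected non-bleeding SAEs, and even these enter the semi-annual tables, although there they are pooled by class with non-serious events.

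A second reply is that the threshold and the arm size limit detection as much as pooling does. This also stands: 31% is the best figure for any Table 8 event, and at 33 per arm it is 5%. Finer tables with the same p-value rule would therefore not be enough.

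A reader might infer two stronger points that the protocol does not support. One is that a specific harm would hardly ever trigger the alert. That depends on a background rate the protocol does not give. At b = 5% the headache figure is 17%, a 30% v 4% harm at b = 20% still alerts 42% of the time, and an event that dominates its class loses little. The other is that the final analysis would test each named harm individually, so that the interim rule alone is blind to it. Section 11.3 compares only events occurring in more than 10% of subjects, that is at least 14 of 132. At Table 8 rates headache would reach that with probability 45%, flushing with about 1%, and abnormal vision essentially never.

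**Conclusion.** The point holds as a weakness in the alert rule, not as an error or contradiction in the protocol. Testing only at the highest MedDRA level reduces the chance of flagging a harm of the Table 8 headache size from 31% to about 3% to 11% at full enrolment. This rests on an assumed independent class background of 10% to 40%; a lower background reduces the loss and a higher one increases it. Power is low at interim looks at either level. Pooling matters little for very large harms, and preferred-term testing alone would not detect rare ones. The practical consequence is greatest for expected non-bleeding SAEs, because there the diluted test decides whether a quarterly report is filed at all. This is worth correcting as a cheap improvement.

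**What to change.** Keep the class-level tables and make two additions to sections 13.8.1 and 13.8.2 and to Table 12.

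1. Apply the same Fisher flag (p<0.01, sildenafil higher) at MedDRA preferred-term level, or to a short prespecified list. Candidates from the protocol's own concerns are priapism with males only in the denominator, visual change, hypotension, headache or facial edema, vaso-occlusive crisis, and acute chest syndrome. Serious bleeding already has a case-by-case alert.
2. Give the DSMB by-arm counts for that list at each quarterly and semi-annual look without any p-value condition. This is needed because the flag cannot fire below 8 v 0.

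The cost is a paragraph of text and a few more tables from data the DCC already codes. False alerts are about 0.3% or less per test per look, and far fewer for rare terms. A flag leads only to further analysis and a note to the DSMB.
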